### Statistical Analysis

Descriptive statistics will be used to describe patient demographics, safety, and SAE of hAECs. The dose–response curve for estimating the MTD is performed using the BOIN package (20). This method computes the probability of toxicity (>0.3) given data base on the list of the number of patients treated at each dose and the number of toxicity at each dose. The MTD is denoted by a marked rise in the probability of toxicity from baseline.

### Data and Safety Monitoring Board (DSMB)

The DSMB will be composed of stroke physicians with experience in clinical trials. Similar to other stem cell trial, after the last subject in cohort 1 (dose 2 million cells/kg) has been observed for 7 days after infusion, the DSMB will evaluate the dose-limiting toxicity (DLT) and other safety information for the eight subjects to determine whether it is safe to proceed to cohort 2.

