## Method

### Overall Plan

We have designed an open label Phase 1 dose escalation trial of hAECs in patients with ischemic stroke with the primary aim of determining the maximal tolerated dose (MTD). Assessment of adverse events will be undertaken blinded to cell dose. Fifteen patients will be recruited for a dose escalation trial in 2018. The final follow-up for the 15th patient in the hAEC arm will be done 12 months after cell delivery. The trial will be submitted to the Monash Health Human Research Ethics Committee.

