### Treatment Doses

Treatment doses are of stage-wise dose escalation: 2, 4, 8, 16, and 32 million cells/kg.

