### Sample Size

This trial is designed as a balance between finding the MTD and finding the effective dose (19). The dose escalation and de-escalation stages are performed similar to the classic 3 + 3 scheme in a Phase 1 trial whereby the sample size is increased in small increments of 3. For a 5-dose escalation, the estimated sample size is 15. The Bayesian Optimal Interval Design (BOIN) (20) used here weighs the dose escalation by the lower boundary of the target toxicity rate (safety rate = 0.6 × target) and de-escalation by the upper boundary (toxicity rate = 1.4 × target). This method recommends setting the default target rate at 0.3 rather than a lower value because of the small sample size typical for Phase 1 trial (20). This default is higher than 90-day mortality of 15.7% for patients at the Monash Medical Centre with NIHSS between 6 and 15. The map of this approach is provided in Figure 2 and Table 1. The rows show that the decision for escalating or de-escalating the dose can be performed by counting the number of patients with the observed toxicity.

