**Figure 2 F2:**
[figure not shown]
Schematics of dose escalation and de-escalation.

**Table 1 T1:** Schematics of escalation and de-escalation dose [dose-limiting toxicity (DLT)].

Human amniotic epithelial cell dose (million cells/kg)	2	2	2	4	4	4	8	8	8	16	16	16	32	32	32
Patient number	1	2	3	4	5	6	7	8	9	10	11	12	13	14	15
Escalate drug dose if number of patients with DLT is ≤	0	0	0	0	1	1	1	1	2	2	2	2	3	3	3
De-escalate drug dose if number of patients with DLT is ≥	1	1	2	2	2	3	3	3	4	4	4	5	5	6	6
Stop trial if number of patients with DLT is ≥	NA	NA	3	3	4	4	5	5	5	6	6	7	7	8	8

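### The DSMB decision to open cohort 2 refers to eight subjects, but the sample-size section and Table 1 put three patients in cohort 1

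*Protocol article*

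**What the plan says.** Under Data and Safety Monitoring Board, the protocol article times the first review by an event: "after the last subject in cohort 1 (dose 2 million cells/kg) has been observed for 7 days after infusion". The board then looks at DLT and "other safety information for the eight subjects to determine whether it is safe to proceed to cohort 2".

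The other statements on numbers are these:

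- Treatment Doses lists "stage-wise dose escalation: 2, 4, 8, 16, and 32 million cells/kg".
- Sample Size says that "the sample size is increased in small increments of 3", and then: "For a 5-dose escalation, the estimated sample size is 15".
- Overall Plan says: "Fifteen patients will be recruited for a dose escalation trial in 2018".
- Table 1 has a dose row ("Human amniotic epithelial cell dose (million cells/kg") above a patient-number row. Patients 1 to 3 stand under 2, patients 4 to 6 under 4, patients 7 to 9 under 8, patients 10 to 12 under 16 and patients 13 to 15 under 32.

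**The concern.** When the last cohort 1 patient reaches day 7, the design as tabulated has treated three patients. Patient 8 in Table 1 belongs to the third dose level, which is reached only after the decision in question. The DSMB sentence therefore counts people whom the rest of the article does not place in cohort 1.

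The primary aim is the maximal tolerated dose, and this is the one DSMB review before escalation that the article describes. The number reviewed determines how far a clean result can rule out a high DLT rate. If the board works from Table 1, it may also determine which decision boundary applies. A reader of the article would think the first escalation rests on more than twice as many patients as the design supplies.

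**Working it through.** **Inputs.** Five doses (Treatment Doses); increments of 3 and a total of 15 (Sample Size, Overall Plan); eight subjects at the first review (DSMB section); target toxicity rate 0.30, with multipliers 0.6 and 1.4 (Sample Size); decision rows (Table 1).

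**1. The plan's own total.** 5 doses × 3 patients = 15. This reproduces the stated figure.

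**2. Can eight be fitted in?**

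- Eight in cohort 1 and three at each later dose: 8 + 4 × 3 = 20.
- Eight in every cohort: 5 × 8 = 40.
- First dose repeated in increments of 3: 3, 6, 9, 12 or 15, never 8.
- Cumulative count at the end of cohort 1: 3.
- Treated patients plus controls: Overall Plan mentions an hAEC arm and Results a control group, but the trial is an open-label dose escalation in 15 patients and the article allocates no concurrent controls.

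None of these yields eight at the first review within the stated design.

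**3. Evidence behind a clean first cohort.** With zero DLTs in n patients, the one-sided 95% upper limit is 1 − 0.05^(1/n).

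- n = 3: 1 − 0.05^(1/3) = 0.63.
- n = 8: 1 − 0.05^(1/8) = 0.31.

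Three clean patients leave DLT rates up to about twice the 0.30 target compatible with the data. Eight would bring the limit down to about the target.

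**4. Table 1 boundaries.** The target is φ = 0.30, with φ1 = 0.6 × 0.30 = 0.18 and φ2 = 1.4 × 0.30 = 0.42.

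- Escalation: ln[(1 − φ1)/(1 − φ)] / ln[φ(1 − φ1)/(φ1(1 − φ))] = ln(0.82/0.70) / ln(0.246/0.126) = 0.2365.
- De-escalation: ln[(1 − φ)/(1 − φ2)] / ln[φ2(1 − φ)/(φ(1 − φ2))] = ln(0.70/0.58) / ln(0.294/0.174) = 0.3585.

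Multiplying by n, then rounding down for escalation and up for de-escalation, reproduces both rows in all 15 columns. The stop row is also reproduced, using a Beta(1,1) prior and a posterior probability above 0.95 that toxicity exceeds 0.3. The article does not state that prior or cut-off, so both are assumptions.

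Taking the column number as the number of patients treated (also an assumption):

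| n | Escalate if DLTs ≤ | De-escalate if DLTs ≥ | Stop if DLTs ≥ |
|---|---|---|---|
| 3 | 0 | 2 | 3 |
| 8 | 1 | 3 | 5 |

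One DLT meets the escalation rule at n = 8 but not at n = 3. Three DLTs stop the trial at n = 3 but only de-escalate at n = 8.

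**5. Chance of meeting the escalation rule, on the same reading.** At a true DLT rate of 0.30:

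- n = 3, no DLT: 0.7³ = 0.343.
- n = 8, at most one DLT: 0.7⁸ + 8 × 0.3 × 0.7⁷ = 0.058 + 0.198 = 0.255 (computed before rounding).

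At a true rate of 0.42 the two figures are 0.195 and 0.087. At 0.157 (the rate that Sample Size quotes for 90-day mortality) they are 0.599 and 0.635.

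**The case against.** The strongest reply is that this is a slip in a count and that nothing operational hangs on it. Several parts of that reply stand.

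- The review is triggered by an event, day 7 after the last cohort 1 infusion. A board can meet then whatever the cohort size. A reader might infer that the review cannot take place; the text does not support that.
- The DSMB section does not send the board to Table 1. As printed, the eighth column is patient 8 at 8 million cells/kg, not an eighth patient at the first dose. The boundary contrast therefore depends on reading columns as numbers treated, which the article does not say.
- A reader might compare the chances of seeing no DLT at a rate of 0.30, which are 34% with three patients and 6% with eight (0.7⁸ = 0.058). That is the wrong contrast on Table 1's own rule, which allows one DLT at n = 8. The relevant figures are 34% and 26%.
- A reader might also infer that the later dose steps go unreviewed. The article names only the step to cohort 2, but a condensed article may leave later meetings to the full protocol or DSMB charter, and Table 1 gives decision rows across all five doses.
- The total of 15 is called an estimate, so the sums of 20 and 40 show that eight does not fit the plan but are not a separate error.

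The inconsistency itself remains. The number is written out as a word in an intact sentence, so it is neither an extraction fault nor an omission. The sentence opens by likening the procedure to another stem cell trial, so the figure may have been carried over, but the article does not confirm that.

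**Conclusion.** The point holds as an internal contradiction in a safety-review sentence: eight subjects in the DSMB section against three in Sample Size and Table 1, with no reading of the article that reconciles them. That part rests on counting alone.

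Its firmest consequence is the strength of evidence at the first escalation. After a clean cohort the upper limit for the DLT rate is 0.63 with three patients and 0.31 with eight, which assumes only independent patients with a common DLT rate. The differences in decision boundary, and the 34% against 26%, hold only if Table 1 is read by number treated.

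The contradiction does not disturb the sample-size arithmetic or the boundaries, both of which reproduce. It does not show that the review is impossible or that later escalations lack oversight.

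**What to change.** Reconcile the DSMB section with Overall Plan, Sample Size and Table 1, so that the first review, the cohort size and the decision boundaries all refer to the same number of patients. The sponsor and DSMB should settle which figure is operative; the article alone cannot decide it.

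If the figure in the DSMB section is the one that changes, the cost is one corrected sentence, carried into the DSMB charter if it appears there. If eight is intended, cohort size, Table 1 and the total of 15 would have to be reworked to match.

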### Human Amniotic Epithelial Cells

The Cell Therapies and Regenerative Medicine Platform (CTRMP) at the Monash Health Translation Precinct has a cryobank of isolated, screened, and stored hAECs for clinical trial use (21). These cells are routinely obtained from healthy women with a healthy singleton pregnancy undergoing an elective cesarean section at term and donating their placenta for clinical trial purposes with informed consent. The donor-screening process involves a two-page medical history questionnaire and viral serology testing. The hAECs are isolated in compliance with current Good Manufacturing Practices using the Biospherix Xvivo cell isolator located at the CTRMP. The manufacturing process is undertaken free of animal-based products, and the isolated cells are cryopreserved without culture expansion. An aliquot of the isolated cells is subjected to microbial and endotoxin testing as part of the cell release protocol (below).

The release criteria for the hAECs are as follows (22):
Absence of microbial contamination and endotoxins.>96% epithelial cells—determined by flow cytometric analysis of EpCAM expression.<1% mesenchymal stromal cells and leukocytes—determined by flow cytometric analysis of CD90, CD105, and CD45.>80% post-thaw viability.>50% reduction in T cell proliferation index.>25% reduction in M1 (CD86^+^) macrophages and >10-fold increase in M2 (CD206^+^) macrophages—determined by macrophage polarization assay.

### Clinical Outcomes (Aim 1)

The primary clinical outcome is safety or frequency of SAEs. The secondary clinical outcome is the patients’ stroke severity (measured by NIHSS) and the level of disability (measured by modified Rankin scale) at 1 week and 90 days. The modified Rankin scale is a widely used tool for measuring outcome in stroke trials. A score of 0 indicates no disability and 6 indicates death. Neurological impairment and functional scores will be measured by a neurologist. The NIHSS will be assessed before the acute study, then again at 24 h, at time points coinciding with MRI scanning (1 week, 1 month, and 12 months), and at any other time during the hospital stay if there is a clinical deterioration. *The neurological and safety outcome assessment will therefore be performed by a blinded observer. This observer will not be involved in patient recruitment*.

### Safety

We define a treatment-emergent adverse effect/AE (TEAE) as any event not present before the initiation of treatment or any event already present that worsened in either intensity or frequency after exposure to the study treatment (23). We classify TEAEs as mild, moderate, severe, or life threatening according to standard procedures (23). DLT is defined here to be equivalent to SAE and includes any untoward effect such as death, life threatening, requires hospitalization (for outpatient), prolonged hospitalization (for inpatients), or requires intervention to prevent permanent damage.

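### The 0.30 DLT target is checked only against 90-day death, not against the background rate of the any-SAE event that drives the dose decisions

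*Protocol article*

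**What the plan says.** The Safety section defines the event: "DLT is defined here to be equivalent to SAE and includes any untoward effect such as death, life threatening". The definition goes on to "prolonged hospitalization (for inpatients), or requires intervention to prevent permanent damage". The neighbouring definition of a treatment-emergent event rests on timing alone: "any event not present before the initiation of treatment or any event already present that worsened in either intensity or frequency". Neither definition asks whether the cells caused the event, and the DLT definition has no observation window.

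The Sample Size section explains the target: "This method recommends setting the default target rate at 0.3 rather than a lower value because of the small sample size". It then adds one comparison with the patient population: "This default is higher than 90-day mortality of 15.7% for patients at the Monash Medical Centre with NIHSS between 6 and 15". The design rates are set by the "lower boundary of the target toxicity rate (safety rate = 0.6 × target") and by "de-escalation by the upper boundary (toxicity rate = 1.4 × target").

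Table 1 bases every escalate, de-escalate and stop decision on the DLT count. The DSMB section has DLT evaluated once the last patient of cohort 1 "has been observed for 7 days after infusion", and states this for cohort 1 only. The Overall Plan follows patients for 12 months and describes an open-label escalation with no concurrent control arm. The Results section mentions a control group when discussing infarct expansion, but the design provides none that would give a background SAE rate.

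**The concern.** The benchmark and the counted event are not the same quantity. Death is one component of the SAE composite, so a target above the death rate need not be above the background rate of the composite. The time frames do not match either: 90 days for the benchmark, 7 days for the one stated DLT review, 12 months for follow-up.

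The patients are acute stroke inpatients, and the Introduction itself describes infection such as pneumonia as a consequence of post-stroke immunosuppression. Such events can be SAEs and would count as DLTs whatever their cause. With no concurrent control, the count cannot separate them from cell toxicity.

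The MTD is the primary aim and is meant to set the Phase 2 dose. If background is high in the chosen window, harmless cells can appear toxic and the MTD is pulled down. If background is low, a 0.30 target leaves room for real excess toxicity.

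**Working it through.** **1. Reproduce Table 1.** Target 0.30, lower design rate 0.6 × 0.30 = 0.18, upper design rate 1.4 × 0.30 = 0.42.

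- Escalation boundary: ln(0.82/0.70) / ln[(0.30 × 0.82)/(0.18 × 0.70)] = 0.2365.
- De-escalation boundary: ln(0.70/0.58) / ln[(0.42 × 0.70)/(0.30 × 0.58)] = 0.3585.
- Escalate at or below n × 0.2365 rounded down; de-escalate at or above n × 0.3585 rounded up. For n = 3 this gives 0 and 2.
- Stop when the posterior probability that the rate exceeds 0.30 is above 0.95, under a uniform prior. The cut-off and prior are assumed.

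All three rows of Table 1 are matched exactly for n = 1 to 15, and 5 doses × 3 patients = 15. The table is arithmetically sound; the issue is what is counted in it.

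**2. Harmless cells, background DLT rate q at every dose.** The article does not give q, so a range is shown. The first cohort escalates only with 0 DLTs in 3, so it fails to escalate with probability 1 − (1 − q)³. The last column is from 40,000 simulated 15-patient trials per rate, applying the Table 1 limits to the count at each dose.

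| q (assumed) | First cohort does not escalate | 2 or more DLTs in 3 | Trial stops at lowest dose |
|---|---|---|---|
| 0.05 | 14% | 0.7% | about 0% |
| 0.157 | 40% | 6.6% | 1% |
| 0.20 | 49% | 10.4% | 3% |
| 0.30 | 66% | 21.6% | 14% |
| 0.40 | 78% | 35.2% | 34% |

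The row at 0.157 is what the article's own figure implies if deaths count to 90 days and no non-fatal SAE occurs: 1 − 0.843³ = 0.401.

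**3. 90-day reading.** Let x be the share of survivors with a non-fatal SAE (not given), and assume that 15.7% applies to eligible patients. Then q = 0.157 + 0.843x.

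- Escalation boundary: (0.2365 − 0.157)/0.843 = 0.094, so x is about 9%.
- Target: (0.30 − 0.157)/0.843 = 0.170, so x is about 17%.
- De-escalation boundary: (0.3585 − 0.157)/0.843 = 0.239, so x is about 24%.

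**4. 7-day reading.** The 15.7% figure is then not the relevant benchmark. Background over 7 days is likely lower than over 90, but no rate is given. As an illustration only, a 7-day background of 0.05 would leave 0.30 − 0.05 = 0.25 between background and target, compared with 0.30 − 0.157 = 0.143 in the article's comparison with death.

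**The case against.** The strongest reply is that 0.30 was never derived from mortality. It is the method's default for small Phase 1 samples, and the mortality comparison is an added reassurance. That is correct, and a reader who inferred that the target rests on 90-day death alone would be misreading the Sample Size section. What stands is that this reassurance is the only clinical one offered, and it concerns a different event.

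A reader might also infer that there is no time frame at all. The DSMB section does state 7 days, for cohort 1. The 7-day reading also fits the recruitment plan better: five cohorts each observed for 90 days need 4 × 90 = 360 days of waiting between cohorts, before any accrual time, while all 15 patients are to be recruited in 2018. On that reading the high-background rows may not apply. But the 7 days are not part of the DLT definition, are not stated for later cohorts, and conflict with the 90-day comparator.

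A third tempting inference is that background events will in fact reach the target. The document does not support that, because x is unknown. Nor is 0.157 a proven floor: the article does not say that this figure reflects the trial's exclusions, such as infarcts above 100 mL or infection at the time of stroke.

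It would also be wrong to treat 0.18 and 0.42 as decision thresholds. They are design rates; decisions turn on 0.2365 and 0.3585.

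Finally, counting every SAE can be a deliberate conservative choice, and the DSMB also weighs other safety information. Dose-blinded assessment would not settle attribution, since every patient receives cells. So the absence of an attribution rule is not itself shown to be an error. It does, however, make the background rate of all SAEs the relevant comparator.

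**Conclusion.** The point holds in limited form and should be fixed. The comparison of 0.30 with 15.7% 90-day mortality does not show that the target exceeds the background rate of the event counted in Table 1, because both the event and the window differ. As written, stroke complications count as toxicity.

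The size depends on a background SAE rate that the article does not give. Across assumed rates from 0.05 to 0.40, harmless cells fail to escalate after the first cohort in 14% to 78% of trials, and the trial stops at the lowest dose in about 0% to 34%. The direction depends on the window: a long window risks an MTD that is too low, and a short one may make 0.30 permissive. These figures assume the same background rate at every dose, independent patients, and Table 1 limits applied to the count at each dose; the stopping results also rest on the assumed 0.95 cut-off and uniform prior. The first-cohort figures are the same if Table 1 is read cumulatively across doses.

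**What to change.** 1. Reconcile the Sample Size, DSMB and Safety sections so that one DLT window applies to every cohort and to the benchmark.
2. Replace the 15.7% death figure with the background rate of the same SAE composite over that window. Take it from the centre's existing records of patients with NIHSS 6 to 15 who meet the eligibility criteria, as far as the records allow. Then confirm or restate the target against it.
3. Have the sponsor state explicitly whether attribution is required for an SAE to count as a DLT. No particular rule is recommended here.

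The cost is a records look-up at the centre that supplied the mortality figure, plus protocol wording. Table 1 needs recalculating only if the target changes. The downside is that the justification for 0.30 may turn out less favourable than it now appears.

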### Imaging Outcomes

The primary imaging outcome is the volume of vasogenic edema at 1 week versus that before treatment. This analysis is performed with a view to assessing safety. The secondary imaging outcome is the change in the infarct expansion ratio (IER) between the outcome post-treatment (T2 FLAIR) infarct volume and the initial DWI infarct volume (see Image Analysis) (16), and symptomatic intracerebral hemorrhage on MR or CT (4). Symptomatic intracerebral hemorrhage is defined by Safe Implementation of Thrombolysis in Stroke Monitoring Study (SIT-MOST) criteria as parenchymal hematoma type 2 (PH2) occurring within 3–6 hours of treatment, combined with neurological deterioration leading to an increase of four points on the NIHSS from baseline, or the lowest NIHSS value after baseline to 24 h (24).

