### Exclusion Criteria

Patients are excluded if (1) eligible for TPA and/or ECR; (2) there is evidence of autoimmune disease, organ transplant, malignancy, splenectomized individuals, or have infection at the time of stroke; (3) neurodegenerative disease such as dementia or Parkinson’s disease; (4) pregnancy; (5) have contraindications for magnetic resonance (MR) imaging such as pacemaker; (6) patients with initial infarct [on diffusion weighted imaging (DWI)] volume of ≤5 or >100 mL will also be excluded (14, 16). This is a common strategy used in many studies to exclude infarcts with very small volume (such as lacunar infarct); very large infarcts are excluded as these patients have a high probability of developing malignant middle cerebral artery infarct and death; (7) patients with mild stroke (NIHSS <6) or very severe stroke (NIHSS >15); (8) blood sugar level of ≤3 or ≥20 mmol/L; and (9) significant lung disease requiring oxygen.

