## Results

The expected outcome from Aim 1 is the MTD to inform the dose to be used in a Phase 2 trial. A smaller vasogenic edema volume, a decrement in infarct expansion, and a decrement in fractional anisotropy volume with dose escalation will provide another assessment of safety and efficacy. It is expected that at the MTD, infarct expansion will be lower than at the preceding doses and in the control group. The immunological assays should parallel our findings in animal experiments (e.g., dampening of the pro-inflammatory cytokines). The findings of the study will be submitted for publication in peer-reviewed journals. Following this, the application will be made to the National Health Medical Research Council to obtain funding for Phase 2 trial.

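### The infarct expansion ratio can carry baseline infarct size into the dose comparison, so the dose reading should adjust for initial DWI volume

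*Protocol article*

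**What the plan says.** Under Imaging Outcomes, the protocol article makes the secondary imaging outcome "the change in the infarct expansion ratio (IER) between the outcome post-treatment (T2 FLAIR) infarct volume and the initial DWI infarct volume". Under Exclusion Criteria, "patients with initial infarct [on diffusion weighted imaging (DWI)] volume of ≤5 or >100 mL will also be excluded", so the reference volume may differ about 20-fold between eligible patients (100/5 = 20).

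The doses are given stage by stage. Treatment Doses lists five levels, and Sample Size says that "the sample size is increased in small increments of 3" and that "For a 5-dose escalation, the estimated sample size is 15". Table 1 lays this out as three patients per dose. Dose follows order of entry and is not randomised.

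The Results section then says how the measure will be read: "a decrement in infarct expansion, and a decrement in fractional anisotropy volume with dose escalation will provide another assessment of safety and efficacy". It adds: "It is expected that at the MTD, infarct expansion will be lower than at the preceding doses and in the control group".

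The Statistical Analysis section covers demographics, safety and the MTD. The article gives no summary statistic, scale or adjustment for the ratio. A condensed article may leave those to the full plan, and their absence is not the point here.

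**The concern.** The article fixes two things: an outcome scale relative to baseline, and a reading of that outcome across doses. The pairing is what causes difficulty. A ratio to baseline removes baseline size only if follow-up volume is proportional to initial volume. If small infarcts grow relatively more than large ones, the ratio falls as baseline rises. Measurement error acts in the same direction, because a fixed error in mL matters far more in a small reference volume than in a large one.

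Nothing in the design balances initial volume across doses, and three patients per dose leave ample room for imbalance. If the later cohorts happen to have larger infarcts, expansion will look lower at higher dose without any effect of the cells. If they happen to have smaller infarcts, a real benefit could be hidden. The Results section counts a fall with dose as efficacy information and leads on to a Phase 2 funding application, so the reading matters even though the outcome is secondary.

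**Working it through.** **Inputs from the article.** Initial DWI volume above 5 and up to 100 mL (Exclusion Criteria); five doses (Treatment Doses); three patients per dose (Sample Size, Table 1). The stated total reproduces: 5 × 3 = 15. The article states no precision or power for the ratio, so there is no further figure to reproduce.

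**Assumed throughout.** IER = follow-up volume / initial DWI volume. This is the natural reading of the name, but the article prints no formula.

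**Step 1: the same growth at different baselines.** With 10 mL of growth, IER = (baseline + 10) / baseline:
- 6 mL: 16/6 = 2.67
- 20 mL: 30/20 = 1.50
- 90 mL: 100/90 = 1.11

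**Step 2: the same DWI error at different baselines.** With a 2 mL error in the denominator:
- 6 mL: 16/8 = 2.0 to 16/4 = 4.0
- 90 mL: 100/92 = 1.09 to 100/88 = 1.14

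**Step 3: two example cohorts, 10 mL growth in everyone, no dose effect.**

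| Baselines (mL) | Mean IER | Median | Geometric mean |
|---|---|---|---|
| 6, 40, 80 | 1.68 | 1.25 | 1.55 |
| 40, 60, 80 | 1.18 | 1.17 | 1.18 |

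One small infarct produces most of the gap in means. The median helps in this example; the geometric mean leaves most of the gap.

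**Step 4: cohorts of three, no dose effect (200,000 simulated; baseline uniform or log-uniform on 5 to 100 mL).**
- Additive growth (10 mL, SD 5): the smallest infarct has the largest ratio in 73 to 75% of cohorts, and mean IER correlates with mean baseline at −0.64 to −0.69.
- Proportional growth (×1.4, log SD 0.3): the smallest infarct has the largest ratio in 33% of cohorts, which is chance, and the correlation is about 0. Two cohort means still differ by at least 1.25-fold in about 37% of pairs, from n = 3 alone.

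**Step 5: whole trials of 15, no dose effect (40,000 simulated).** Assumed: baseline log-uniform 5 to 100 mL, residual log SD 0.3, measurement error SD 2 mL. The comparison is the dose slope of raw IER, relative to its mean, against the dose coefficient from log follow-up volume adjusted for log initial volume. In one set of runs the standard errors and variance ratios are:
- slope 1.0: (0.073/0.070)² = 1.1
- slope 0.8: (0.088/0.066)² = 1.8
- slope 0.6: (0.113/0.063)² = 3.2

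Independent repeats, with 1.4-fold mean growth, give these ranges:

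| Log-log slope | Highest cohort mean IER at least twice the lowest | Variance ratio, raw to adjusted |
|---|---|---|
| 1.0 | 17 to 19% | 1.1 to 1.3 |
| 0.8 | 30 to 31% | 1.7 to 2.1 |
| 0.6 | 54% | 3.0 to 3.9 |

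In a repeat with these assumptions, the false raw-IER dose slope correlates with chance baseline imbalance at −0.20, −0.53 and −0.71 for slopes 1.0, 0.8 and 0.6. After adjustment the correlation is about 0. Using cohort medians does not solve the problem here: they differ at least two-fold in 23%, 33% and 59% of trials, slightly more often than the means.

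**The case against.** The strongest reply is that the article only names an outcome and an expected direction. It specifies no mean of raw ratios, no model and no formula. Its one figure for the measure, under Image Analysis, is a proportion of 75% of patients, which hints at a present/absent use to which the magnitudes above would not apply. Choice of summary and adjustment normally belongs to the analysis plan. This stands in part: the formula is inferred, and no missing model is alleged. But the baseline-relative scale and the cross-dose reading are both stated, and dichotomising would not by itself remove a dependence on baseline.

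A reader might infer that the smallest infarct sets the result. The documents do not support that as a general statement. It needs non-proportional growth or material absolute error, together with a mean of raw ratios; under proportional growth it fails.

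A reader might also infer a systematic bias towards higher doses. There is none. With no treatment effect, the average raw-IER dose slope is about 0. The highest dose has the lowest cohort mean in 20% of trials with or without adjustment, and a fall at every step occurs in about 0.8% with the raw ratio and 0.8 to 1.0% with adjustment. Adjustment therefore does not make a false ordering rarer. When the slope is below 1, it makes chance differences smaller and uncouples them from baseline size.

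Finally, the outcome is secondary, escalation and stopping use DLT counts, and the eligibility limits already remove the most unstable denominators. All of that stands and limits the consequence.

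**Conclusion.** The point holds in a limited form. The ratio can depend on initial infarct volume, and with three patients per sequential dose level a chance difference in that volume can be read as a dose effect. The harm is confounding by chance imbalance and lost precision. Its size depends on how growth relates to baseline: close to nothing at a log-log slope of 1.0, rising to a three- to fourfold variance penalty at 0.6. No section gives the growth pattern, segmentation error or baseline distribution, so these figures show a plausible range and are not estimates for this trial. Dose escalation, the MTD and the sample size of 15 are unaffected. The change is still worth making because the needed baseline is already measured.

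**What to change.** Base the dose reading in the Results section on a baseline-adjusted analysis: log follow-up infarct volume as response, log initial DWI volume as covariate, and dose level as an ordered term, over all treated patients, at whichever follow-up scan the outcome uses. Report the dose coefficient with its confidence interval and label it exploratory.

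Keep the expansion ratio as a descriptive measure. State its formula, and show it for each patient beside the initial volume, the follow-up volume and the absolute growth in mL. Do not rely on a geometric mean or a median to remove the dependence on baseline.

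This uses the same two volumes and needs no additional scans, patients or changes to eligibility. It costs one degree of freedom among 15 patients and gains almost nothing if growth is exactly proportional. It will not rescue the precision of cohorts of three, so the result should still be read as a signal only.
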